### Sample Size

#### Objective 1

Using the number of deliveries and maternal and perinatal deaths in 9 regional and district facilities in the chosen intervention catchment areas (the Eastern Cape, Limpopo, and Mpumalanga) between 2018 and April 2019, rates were found to be 115.4 maternal deaths per 100,000 live births, 14.4 neonatal deaths per 1000 live births, and 22.5 stillbirth births per 1000 facility births. For this study, an intraclass correlation estimator from a random intercept logistic regression model was used. Using the average facility size (based on deliveries in the intervention catchment areas during the baseline period), the variance inflation factor was estimated at 1.0, 1.4, and 1.3 for the maternal mortality ratio, neonatal mortality rate, and stillbirth rate, respectively. To test the hypothesis that there was no improvement against a 50% increase in the baseline, with 80% power at a 5% two-sided significance level, the number of live births would be 40,524 and 4512 for testing maternal and neonatal mortality rates and 2666 for stillbirth rates. We will observe at least 41,000 deliveries pooled across the 3 catchment areas over a 3-year period to have minimum power for all outcome comparisons. The same would accrue in the control facilities.

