
### Statistical Analysis

#### Objective 1

The institution maternal and perinatal mortality indicators will be calculated using DHIS data. Trend in iMMR, neonatal mortality rate, and stillbirth rates (with SE bars) during the pre- and postintervention periods will be disaggregated by intervention arms. RR and 95% CI will be calculated along with data on confounding variables, such as antenatal care coverage before 20 weeks, delivery at health facility access by tar road, deliveries of female participants aged <19 years, and deliveries of female participants aged ≥19 years (derived from total deliveries and deliveries of female participants aged <19 years). The trends in mortality and stillbirths will be compared before the COVID-19 pandemic (January 2019-March 2020) and during the COVID-19 pandemic (April 2020-March 2021) and in the context of the COVID-19 waves. The baseline period (2017-2018) will also be provided. Observed numbers and rates will be determined monthly and quarterly across all 9 provinces in the country and overall. To compare the Mphatlalatsane Initiative intervention and control arm trends in mortality, an interrupted time series regression model using Poisson regression model with Newey-West SEs to account for autocorrelation and possible heteroskedasticity will be used.

#### Objective 2

This study will use quantitative descriptive analyses and exploratory factor analysis to examine associations between sociodemographic characteristics, childbirth characteristics, and maternal participants’ experience of health care quality and the health care facility during the antenatal to postpartum period.

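### The pre-COVID window contains January–March twice and the COVID window contains it once, so a pooled before/during rate ratio is not balanced by season; the article also gives two different start dates for the pre-COVID window.

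*Protocol article*

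**What the plan says.** The protocol article (Statistical Analysis, Objective 1) sets the two pandemic periods as "before the COVID-19 pandemic (January 2019-March 2020) and during the COVID-19 pandemic (April 2020-March 2021". It speaks of comparing trends, read against the COVID-19 waves. It adds that "The baseline period (2017-2018) will also be provided" and that "Observed numbers and rates will be determined monthly and quarterly across all 9 provinces in the country and overall". No calendar matching of the two periods is stated.

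The comparison of intervention with control facilities is a separate analysis: "an interrupted time series regression model using Poisson regression model with Newey-West SEs to account for autocorrelation and possible heteroskedasticity will be used".

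The Abstract (Methods) describes a first analysis that combines 18 facilities whatever their allocation, to give a general picture of the pandemic's effect. The Results section then reports single before and during totals for the three provinces. There the before period runs from March 2019 to March 2020, not from January 2019. The Abstract and Discussion interpret these totals as a rise in maternal and neonatal deaths with stillbirths about unchanged.

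**The concern.** Dividing deaths by births corrects for the unequal length of the windows but not for their unequal calendar mix. If any of the three rates tends to be higher or lower in January–March, the before period is weighted towards that season and the during period is not. A pooled ratio then moves away from 1 with no pandemic effect at all. A high January–March rate would hide part of a rise, and a low one would create or enlarge it.

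The pandemic reached every facility, so this contrast has no unexposed series to cancel the shift. At stake is the reading of the pandemic contrast for the two end points with small changes, neonatal mortality and stillbirth.

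The conflicting start date adds a second problem: a reader cannot tell which before period produced the reported totals.

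**Working it through.** **1. The plan's own figures.** The article states no seasonal figure, so there is none to reproduce. The effect it is sized on serves as one yardstick. Inputs from Sample Size, Objective 1: baseline rates "115.4 maternal deaths per 100,000 live births, 14.4 neonatal deaths per 1000 live births, and 22.5 stillbirth births per 1000 facility births"; for variance inflation, "the variance inflation factor was estimated at 1.0, 1.4, and 1.3"; 80% power, two-sided 5%. The standard two-proportion formula for a halving of the rate, multiplied by the inflation factor, gives 40,773 / 4,528 / 2,674 births per group. The article states 40,524 / 4,512 / 2,666. The agreement is within 1%, so the design effect is a 50% change (the figures correspond to a reduction).

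**2. Window composition** (dates from Statistical Analysis, Objective 1).
- Before, January 2019–March 2020: 15 months, 6 of them January–March, 6/15 = 0.40.
- During, April 2020–March 2021: 12 months, 3 of them January–March, 3/12 = 0.25.

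**3. Spurious rate ratio.** Let January–March rates be (1+s) times those of the other months. Assume equal births per month, a stable yearly pattern and no pandemic effect. The before mean is 1+0.40s and the during mean is 1+0.25s, so

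spurious RR = (1+0.25s)/(1+0.40s).

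The values of s are assumptions.

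| s | Spurious RR | Shift |
|---|---|---|
| +2% | 1.005/1.008 = 0.997 | −0.3% |
| +5% | 1.0125/1.020 = 0.993 | −0.7% |
| +10% | 1.025/1.040 = 0.986 | −1.4% |
| +20% | 1.050/1.080 = 0.972 | −2.8% |
| −10% | 0.975/0.960 = 1.016 | +1.6% |
| −20% | 0.950/0.920 = 1.033 | +3.3% |

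A smooth yearly cycle gives similar sizes: an amplitude of 5% gives at most 0.9%, and 10% at most 1.9%, over all possible peak months.

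**4. Changes to set this against** (counts from Results; 1,093,372 and 1,037,528 live births).
- Maternal: 1024/1,093,372 = 93.7 and 1315/1,037,528 = 126.7 per 100,000; ratio 1.353.
- Neonatal: 13,095/1,093,372 = 11.98 and 13,026/1,037,528 = 12.55 per 1000; ratio 1.048, simple Poisson 95% CI 1.02–1.07.
- Stillbirth: 22,030/(1,093,372+22,030) = 19.75 and 20,891/(1,037,528+20,891) = 19.74 per 1000 births; ratio 0.999, 95% CI 0.98–1.02.

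A 1.4% shift (s = 10%) is 1.4/35.3 = 4% of the maternal change and 1.4/4.8 = about 30% of the neonatal change. It exceeds the stillbirth change of −0.06%. Against a 50% effect it is 1.4/50 = about 3%.

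**5. The window named in Results.** March 2019–March 2020 is 13 months with 4 in January–March, 4/13 = 31%. The spurious ratio becomes (1+0.25s)/(1+(4/13)s): 1.025/1.0308 = 0.994 at s = 10% and 1.050/1.0615 = 0.989 at s = 20%. For the reported neonatal change this is 0.6/4.8 = about 12% and 1.1/4.8 = about 23%. The live births per month are 72,891 if divided by 15 and 84,106 if divided by 13, against 1,037,528/12 = 86,461 in the during period. The totals therefore look more like the 13-month label than the 15-month one, though this does not settle it.

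**6. Matched windows.** April 2019–March 2020 and April 2020–March 2021 each contain every calendar month once. The ratio is (1+0.25s)/(1+0.25s) = 1.000 for any s.

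**The case against.** The strongest reply is that nothing in the documents shows seasonality of any size in these rates. A reader might infer that ordinary seasonality shifts the contrast by 1–3% as a matter of fact. The documents do not support that. Such a shift needs January–March to differ from other months by roughly 6–22%, and at 2–5% it is only 0.3–0.7%. This objection stands, so the size can only be given conditionally.

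Second, a reader might infer that the shift is a large part of the change sought. That fails for maternal mortality and for the 50% effect the study is sized on. It is arguable only for the small neonatal change and the near-null stillbirth change. Even there the reported counts carry the 13-month label, under which the shift is less than half as large.

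Third, the article speaks of trends, with monthly and quarterly rates and 2017–2018 alongside. It does not spell out one pooled ratio over these windows. That is fair, but the Results give pooled totals and the Abstract and Discussion draw conclusions from them, so the pooled contrast is in use.

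Fourth, a reader might fault the time-series model for naming no seasonal term and note that Newey-West errors do not correct a point estimate. The documents do not support this as a finding. That model is assigned to intervention versus control, where proportional seasonality common to both arms cancels. A seasonal term may also sit in an analysis plan that is not shown.

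**Conclusion.** The point holds in a limited form. The stated windows are unbalanced by calendar quarter (40% against 25%), and any pooled before/during ratio over them inherits a seasonal shift of (1+0.25s)/(1+0.40s). The shift is of unknown size: about 0.3% to 2.8% for assumed January–March excesses of 2% to 20%, with slightly larger shifts in the other direction for deficits of the same size. This rests on equal monthly births and a stable seasonal pattern.

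It is minor for maternal mortality and irrelevant to the 50% design effect. It could colour the interpretation of the neonatal and stillbirth contrasts, whose simple Poisson 95% half-widths are themselves only about 2%. It does not undermine the intervention-versus-control comparison.

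The disagreement between January 2019 and March 2019 as the start of the pre-COVID period is a plain inconsistency, whatever the seasonal pattern.

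**What to change.** For the pooled pandemic rate ratios, compare April 2019–March 2020 with April 2020–March 2021. State one definition of the before period and use it in both Statistical Analysis and Results; if the reported totals came from another window, relabel or recompute them.

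No new data are needed. The matched months fall inside every extraction or analysis range the article gives (2017–2022 in Data Sources, 2019–2022 in Table 1, 2019–2021 in Study Design).

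The cost is three months of the simple before window. With equal expected events per month, the standard error of the log ratio rises by the factor √[(1/12+1/12)/(1/15+1/12)] = √(0.1667/0.15) = 1.05, about 5%. The dropped months can stay in the trend displays and the time-series model. A calendar-month or quarter term in that model is a suggestion only.

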### Eligibility Criteria and Recruitment of Facilities

#### Overview

The intervention facilities were purposively identified by the National Department of Health (NDOH) as sites with MNH service performance and capacity below the national average in South Africa. In addition, the selected intervention sites reflect the clinical and referral pathways and represent both urban and rural settings. For objectives 2 and 3, the comparison districts were purposively selected to match the intervention districts in as many respects as possible, including iMMR, stillbirth rate, neonatal mortality rate, sociodemographic characteristics, service organization, and setting (rural, urban, and periurban), and to provide the NDOH standard of care. In total, 3 facilities (2 district hospitals and 1 regional hospital) in the comparison district were selected and matched to the intervention district based on the total number of births. Data collection for objectives 2 and 3 is conducted in 18 hospitals (15 district- and 3 regional-level hospitals). Objective 4b is being conducted in 15 hospitals, purposively selected from the 21 intervention facilities.

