### Data Sources

#### Objective 1

Mortality data from 2017 to 2022 were extracted from the District Health Information System (DHIS; Table 1).

**Table 1 table1:** Mphatlalatsane data sources.

Objective	Data source	Variable or theme	Level of analysis
1	DHIS^a^	Mortality data (maternal, neonatal, and stillbirths) extracted quarterly from 2019 to 2022	District and facility
2	Participant interview shortly after delivery in regional or district hospitals	The effect of the QI^b^ intervention over time on patients’ experience of the quality of antenatal and postnatal health care services from 2021 to 2022	Individual
3a	Maternal records from regional or district hospitals	Facility audit of maternal records will be conducted to measure adherence to clinical protocols on normal pregnancy, HIV, eclampsia, and postpartum hemorrhage from 2021 to 2022	Individual
3b	Structured observation checklists will be interviewer administered in selected facilities based on the Newborn QI Toolkit norms and standards for newborn care, which were developed to collect data in each facility [23]	Availability of equipment and supplies Availability of guidelines or policies Distribution and availability of drugs Data quality and use Staffing Infrastructure	Facility
4a	Semistructured interviews and FGDs^c^ with the QI advisers, operational managers, and management staff	Stakeholder analysis: coordination processes, nature and quality of social networks, decision-making processes, formal and informal communication, and collaboration between key actors. We will set up monthly individually open-ended debriefing meetings with the QI advisers, and they will reflect on their work and engagement with the QI teams. We will also review program documentation, including the documentation that the QI teams will generate during the PDSA^d^ cycles. We will also conduct other program meetings at the macro- and mesolevels.	National, provincial, district and subdistrict

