#### Objective 2 and 3a

Literature on patient satisfaction in South Africa is scarce; in other studies, patient satisfaction varies from <50% to as high as 75% [25]. The impact of the intervention on patient satisfaction may likely be less compared with that before the COVID-19 era because of disruptions in service delivery. For the 18 facilities in the intervention arm and 18 facilities in the control arm, at a power of 80%, and an expected increase in patient satisfaction from 50% to 60%, given an intraclass correlation coefficient of 0.06, the number of pregnant women required is 102, with a total sample size of 1529 per arm in the pre- and postintervention periods.

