#### Objective 3a and 3b

Quantitative data analysis will be conducted on demographic data as well as specific management elements offered to participants with hypertension in pregnancy and primary postpartum hemorrhage based on predetermined criteria [28]. Patients with normal pregnancies will be scored against the NDOH clinic checklist for booking and follow-up of patients without HIV [29]. A study nurse will allocate the score based on antenatal and intrapartum data abstracted from maternity records. The scoring system will be as follows: for any variable that is fully met, 1 unit will be awarded; if partially met, half of a unit will be awarded; whereas if absent, 0 will be awarded. If a patient is managed for more than one of the specific complications, each entity will be assessed separately. The criteria scores for each patient will be individualized. The level of care for each complication will then be assessed as follows:

*Care score/Criteria score × 100*

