### Maternal Satisfaction With Care

From October 27, 2021, to July 8, 2022, there were 3934 completed maternal interviews across 18 hospitals. In the maternal interviews, participants were largely satisfied with their antepartum care (3556/3841, 92.58%). Approximately 5.88% (226/3841) of the participants self-reported complicated deliveries.

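### Objectives 2 and 3a are sized as a facility-clustered two-arm comparison, but the named analyses neither deliver that comparison nor carry the hospital clustering

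*Protocol article*

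**What the plan says.** - **Sizing** (Protocol article, Sample Size, Objective 2 and 3a). The calculation sets 18 intervention facilities against 18 control facilities, with 80% power for a rise in satisfaction from 50% to 60%. It continues: "given an intraclass correlation coefficient of 0.06, the number of pregnant women required is 102", and "with a total sample size of 1529 per arm in the pre- and postintervention periods".
- **Purpose and level** (Table 1). The objective 2 row describes the effect of the quality improvement intervention over time on women's experience of care. The objective 3a row reads "Facility audit of maternal records will be conducted to measure adherence to clinical protocols". The level of analysis is *Individual* in both rows. It is district and facility for objective 1, and facility for objective 3b.
- **Analysis** (Statistical Analysis). For objective 2: "This study will use quantitative descriptive analyses and exploratory factor analysis to examine associations between sociodemographic characteristics, childbirth characteristics", with maternal experience of care as the other side of the association. For objective 3a: "Quantitative data analysis will be conducted on demographic data as well as specific management elements", followed by a care score for each patient.
- **Design** (Eligibility Criteria and Recruitment of Facilities, Overview). Intervention sites were chosen by the health department. Comparison districts were chosen to resemble the intervention districts, and three comparison facilities "were selected and matched to the intervention district based on the total number of births". Data for objectives 2 and 3 come from 18 hospitals.
- **Data so far** (Results, Maternal Satisfaction With Care). "there were 3934 completed maternal interviews across 18 hospitals". Satisfaction with antepartum care is 3556/3841, or 92.58%, printed without an interval.

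**The concern.** The sizing, the stated purpose and the analysis text do not describe the same analysis. The sizing is for an arm contrast with women clustered in facilities. Descriptive analysis and exploratory factor analysis do not estimate or test that contrast, and a care score is an outcome rather than a comparison. The clustering that was allowed for in the sample size does not reappear.

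Following the text therefore leads to one of two results. Either the sized comparison is not made, or it is added later with nothing in the plan to say that hospital must enter it. In the second case ordinary differences between hospitals could be reported as an effect of the Initiative, of hospital level or of setting. These are secondary end points, but the abstract says the results will inform scale-up.

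**Working it through.** **Inputs**
- ICC 0.06, from the sample size for objectives 2 and 3a.
- 102 women. The text gives no unit; I read it as per facility.
- 3841 women with a satisfaction answer in 18 hospitals: 3841/18 = 213.4 per hospital. Counts by hospital are not given, so equal sizes are assumed.
- 5% two-sided. The protocol states this for objective 1; it is assumed here.
- Nine hospitals per arm in the simulations (assumed equal split of 18).

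**1. The plan's own figure.** For 50% versus 60%, 80% power and 5% two-sided, an unclustered comparison needs 388 women per arm. With design effect 1 + (m − 1) × ICC:
- m = 102: 1 + 101 × 0.06 = 7.06, and 388 × 7.06 = 2739, not 1529.
- m = 50 (not stated anywhere): 1 + 49 × 0.06 = 3.94, and 388 × 3.94 = 1528.7.

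So 1529 is not reproduced from the stated 102, although it does match a clustered calculation with 50 per facility. That inconsistency is a separate matter. It matters here only because it adds a third candidate cluster size.

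**2. Cost of ignoring hospital in a hospital-level contrast.** The standard error is too small by √DEFF. A nominal 5% test then has true size 2 × [1 − Φ(1.96/√DEFF)].

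| Women per hospital | DEFF | √DEFF | True size |
|---|---|---|---|
| 50 (reproduces 1529) | 3.94 | 1.98 | 32% |
| 102 (stated) | 7.06 | 2.66 | 46% |
| 213.4 (analysed, objective 2) | 13.74 | 3.71 | 60% |

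Simulation of 9 versus 9 hospitals with beta-binomial outcomes agrees: 45–48% at 102 and 59–61% at 213, for satisfaction of 50% or 92.58%. A t test on hospital-level proportions holds 4–6%. Another simulation, with normally distributed hospital rates cut off at 0 and 1, gave 42% and 55% at 92.6% satisfaction.

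**3. The reported percentage.** The independent half-width is 1.96 × √(0.9258 × 0.0742/3841) = 0.83 points. Clustered, it is 0.83 × 3.71 = 3.1 points. The effective sample size is 3841/13.74, about 280.

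**4. Sensitivity.**
- ICC 0.01 to 0.10 (assumed range): true size 17–56% at 102 per hospital and 27–68% at 213.
- Half of the ICC lying between provinces balanced across arms (assumed): 33% at 102 and 48% at 219 (3934/18).
- A characteristic that varies within hospitals, with ICC 0.06: about 5% when its prevalence is the same everywhere, and 8–13% when prevalence ranges from 30% to 70% between hospitals (assumed).

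**The case against.** The strongest reply is that the article commits no error. It nowhere says that women will be treated as independent. *Individual* in a table of data sources may simply name the unit of the data, and a mixed model with a hospital random intercept is itself an individual-level analysis. The authors know about clustering, since they use an intraclass correlation in both sample-size paragraphs. Model detail is commonly left to an analysis plan, which is not shown here. The association aim for objective 2 concerns sociodemographic and childbirth characteristics, which vary mostly within hospitals.

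Much of this stands. A reader might infer that the plan's intervals are 3.7 times too narrow and that its tests give false positives 46–60% of the time. The documents do not support that. They name no arm test, hospital-type test, interval or significance level for these objectives, and 92.58% is printed without an interval. The two figures also have different bases: 46% goes with a ratio of 2.7, and 3.7 goes with 60%. Nor can 3.7 be carried to objective 3a, for which no record count is given. A reader might also take the hospitals to be matched by province. The protocol lists matching on mortality rates, sociodemographics, service organization, setting and births, and does not name province as a matching factor.

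The reply does not remove the mismatch itself. The level column does separate individual from facility, and *Individual* stands where the ICC was invoked. For objective 1 the same section goes as far as naming Newey-West standard errors for autocorrelation. For objectives 2 and 3a it names methods that do not produce the contrast that was sized. An unseen analysis plan could supply a model, but these sections would still need to be reconciled.

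**Conclusion.** The point holds as an internal mismatch with a conditional consequence. The sized comparison is two-arm and clustered by facility; the named analyses contain neither the arms nor the hospitals.

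If an arm or other hospital-level contrast, or the overall satisfaction percentage, is analysed with women as independent, then at ICC 0.06 standard errors are about 2.7 times too small at 102 women per hospital (46% false positives for a test). For objective 2 they are about 3.7 times too small at 213 per hospital (60%; half-width 3.1 rather than 0.8 points). This rests on the plan's ICC, equal hospital sizes and a 5% two-sided test. A smaller ICC or effective matching lowers the inflation, but every hospital-level scenario examined stays well above 5%. Associations with within-hospital characteristics are only slightly affected. For objective 3a the direction is the same, but its size at the achieved record count cannot be computed. The change should be made; these are secondary end points, and nothing already reported is shown to be wrong.

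**What to change.** 1. In Table 1, change the level of analysis for objectives 2 and 3a to individual, clustered by hospital.
2. In the analysis text for objectives 2 and 3a, name the intervention-versus-control contrast for satisfaction and for care scores.
3. Base its tests and intervals on the hospital as the unit of inference: either a mixed model with a hospital random intercept and small-sample degrees of freedom, or a t test on hospital-level means across the 18 hospitals. Apply the same rule to other hospital-level factors.
4. Report the observed ICC, and attach cluster-adjusted intervals to reported percentages, including the 92.58%.

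A province or matched-set term is optional. Any gain depends on how much between-hospital variance it explains, which the document does not give; a province term would use 2 degrees of freedom.

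The cost is a change of wording, with no new data collection, provided the hospital is recorded for each interview and record. The downside is wider intervals and fewer nominally significant results.

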**Objective:**

Our evaluation aims to determine the effect of various exposures, including the COVID-19 pandemic, and a system-level, complex, patient-centered quality improvement (QI) intervention (the Mphatlalatsane Initiative) on maternal and neonatal health services at 21 selected South African facilities. The objectives are to determine whether Mphatlalatsane reduces the institutional maternal mortality ratio, neonatal mortality rate, and stillbirth rate (objective 1) and improves patients’ experiences (objective 2) and quality of care (objective 3). Objective 4 assesses the contextual and implementation process factors, including the COVID-19 pandemic, that shape Mphatlalatsane uptake and variation.

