### Study Aims and Objectives

The evaluation primarily aims to measure the effectiveness of the Mphatlalatsane Initiative on iMMR, neonatal mortality rate, and stillbirth rate (objective 1). We also assess whether patients’ experiences of care (objective 2) and quality of maternal (objective 3a) and neonatal care (objective 3b) were affected by the pandemic. Objective 4a explores the macrolevel (regional and national) and mesolevel (subdistrict and district) factors, and objective 4b explores the microlevel (facility) process and contextual factors, including the COVID-19 pandemic, to explain variations in QI uptake and program outcomes and implications for scale-up. Partner interviews (objective 4a) commenced in early 2020, and data collection for objective 4b began in May 2021.

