4b	Interviews and FDGs with QI teams QI team surveys QI adviser debriefings Program documentation	QI advisers, teams, and facility managers: setting up, management structures, systems of communication, translation of their PDSA cycles into everyday practices, climate for QI activities, relational dynamics in the teams, ownership of change, resource use, experiences, and perceptions of implementation changes over time, perceived benefits, and challenges of the QI work in their facilities. QI team outcomes: packaging learning practices for scale-up and identify the “leverage points” for change.	Facility

^a^DHIS: District Health Information System.

^b^QI: quality improvement.

^c^FGD: focus group discussion.

^d^PDSA: Plan-Do-Study-Act.

#### Objective 2

In-person or telephonic interviews were conducted with pregnant women shortly after delivery to measure participants’ subjective experiences of care. The survey used a 5-point Likert scale based on a prior study of maternal patient satisfaction with services in Tanzania [24]. Data collectors administered paper-based surveys at the midline, which were then captured using REDCap (Research Electronic Data Capture; Vanderbilt University) software.

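### Objective 2 gives factor analysis an association question it cannot answer, and neither tool named estimates the intervention effect for which the objective is stated and sized

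*Protocol article*

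**What the plan says.** The Statistical Analysis section gives objective 2 a single sentence. It names quantitative descriptive analyses together with "exploratory factor analysis to examine associations between sociodemographic characteristics, childbirth characteristics, and maternal participants"; the last term is the women's experience of care from the antenatal to the postpartum period. Two tools are named, and no other model and no comparison of arms or periods.

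The data are item responses: "The survey used a 5-point Likert scale based on a prior study of maternal patient satisfaction with services in Tanzania" (Data Sources, Objective 2).

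Elsewhere objective 2 is an effect question:

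- The abstract asks whether the initiative lowers mortality "and improves patients’ experiences (objective 2) and quality of care (objective 3").
- Table 1 gives the variable as the effect of the QI "intervention over time on patients’ experience of the quality of antenatal and postnatal health care services from 2021 to 2022", at individual level.
- Study Aims and Objectives has a different wording and asks instead whether the pandemic changed women's experiences.

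The Sample Size section for objectives 2 and 3a plans 80% power for satisfaction rising from 50% to 60%, with an intraclass correlation of 0.06. Outcome Measures lists patient experience as a secondary end point.

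**The concern.** Exploratory factor analysis models the correlations among questionnaire items. It has no outcome and no explanatory variables, so it returns loadings. It gives no estimate, interval or test of how age, HIV status or a complicated delivery relates to experience. The sentence therefore gives a named method a purpose it does not serve.

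That leaves descriptive analysis to carry the objective. Crude tables mix the effects of characteristics that tend to go together, and on their own they treat women from the same hospital as independent. The question that the sample size was built for, a difference in satisfaction due to the intervention, has no estimator among the tools named. If the sentence is followed literally, a secondary end point ends in loadings and unadjusted tables. If it is not, the association and effect models are chosen after the data are in.

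**Working it through.** The plan states no figure to reproduce here. The check is whether each named tool can deliver what is asked of it.

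**1. What factor analysis returns.** Take a latent experience score f = b·x + e, where x is a binary characteristic held by half the women, e has variance 1 and b is the true effect. Let eight items each equal 0.7·f plus 0.7 times independent noise of variance 1. The setup is illustrative, with continuous items.

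- The variance of f is 1 + 0.25·b². That is 1 for b = 0 and 1.0625 for b = 0.5.
- The standardised loading is √[var(f) / (var(f) + 1)].
- For b = 0: √(1/2) = 0.707. For b = 0.5: √(1.0625/2.0625) = 0.718.

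A simulation of 3934 women gave loadings of 0.70 to 0.72 with no effect and 0.71 to 0.73 with an effect of 0.5. The loadings barely move, and nothing in the output estimates b.

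**2. What the descriptive analysis returns.** In the same simulation the difference in mean item score between the two groups was 0.00 for b = 0 and 0.38 for b = 0.5 (expected 0.7 × 0.5 = 0.35). Descriptive tables therefore do show an association. The data had no confounding and no clustering, so this is the best case for a crude contrast.

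**3. What clustering does to a crude contrast.** Inputs: 3934 completed interviews in 18 hospitals (Results, Maternal Satisfaction With Care) and an intraclass correlation of 0.06 (Sample Size). Hospitals are assumed equal in size.

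- Women per hospital: 3934 / 18 = 218.6.
- Design effect for a factor that is constant within hospital, such as arm: 1 + (218.6 − 1) × 0.06 = 14.05.
- Standard error ratio: √14.05 = 3.75. Effective number of women: 3934 / 14.05 = 280.

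To put this on the scale of the planned difference, assume 3934 / 2 = 1967 women per arm and proportions of 50% and 60%.

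- Ignoring clustering, the standard error is √[(0.25 + 0.24) / 1967] = 0.0158, so the 95% half-width is 1.96 × 0.0158 = 3.1 percentage points.
- Allowing for clustering, 3.1 × 3.75 = 11.6 percentage points, which is wider than the 10-point difference planned for.

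For characteristics that vary within hospitals the inflation is smaller.

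**4. Question against tool.**

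| Question for objective 2 | Where stated | Factor analysis | Descriptive analysis |
|---|---|---|---|
| Characteristics and experience | Statistical Analysis | No estimate | Crude only |
| Intervention effect on experience | Abstract; Table 1; sized in Sample Size | No estimate | Not stated; a table by arm would be crude |

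**The case against.** The strongest reply is that the sentence names two tools. Means or proportions of experience by age, parity or mode of birth do describe associations, as step 2 shows. A reader might infer that objective 2 has no analysis that answers its question at all. The document does not support that: a crude answer to the association question is planned. What is missing from the tools named is an adjusted, cluster-aware estimate and the effect comparison.

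A second reply is that a journal article condenses, and the regression that uses the factor scores may stand in a fuller plan. That is fair for model detail, which is not criticised here. It does not cover a stated pairing of method and purpose that is wrong, nor an analysis sentence whose question differs from the one in the abstract and Table 1. The same section does name a full model for objective 1.

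A further inference is tempting. Because 92.58% of women (3556/3841) were satisfied with antepartum care, the factor analysis might be thought distorted by a ceiling and its subscales artefacts. The document does not bear this out. It names no correlation matrix or extraction method, and it does not say whether that percentage is one item, a composite or a recoded rating. It cannot be carried over to all items.

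**Conclusion.** The point holds in a limited form. Exploratory factor analysis is assigned associations it does not estimate. The other named tool gives only crude ones. Neither estimates the intervention effect that objective 2 is stated and sized to measure.

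The conclusion on method fit rests on the text alone. The size of the clustering problem, a design effect of about 14 for an arm comparison, rests on the plan's intraclass correlation and on equal hospital sizes; unequal sizes would generally raise it. The matter concerns a secondary end point and leaves the mortality outcomes untouched. It should be corrected because the remedy is cheap and otherwise the model would be chosen after the data have been seen.

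**What to change.** Reword the objective 2 paragraph so that each method has the task it can do:

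- **Scale:** use exploratory factor analysis only to build the experience score or subscores from the Likert items. An ordinal (polychoric) version is an optional refinement.
- **Associations and effect:** regress the experience score, and the satisfaction proportion used for the sample size, on arm and on sociodemographic and childbirth characteristics. Include a hospital random effect and a method suited to few clusters, since there are only 18 hospitals.
- **Descriptive tables:** keep them as support.
- **Wording:** align the question in the abstract, the aims, Table 1 and the analysis section. The setting is non-randomised and the article dates the objective 2 data to 2021 to 2022, after the intervention began. Unless earlier interviews exist, the arm coefficient should therefore be described as an adjusted between-arm difference and not as a before-and-after effect.

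The cost is one rewritten paragraph and routine models in Stata, the software already named. No new data are needed.
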